## Abstract

•Evaluates an enhanced educational intervention to improve IC acceptance and adherence.•Randomized controlled trial design with three follow-up time points (T0, T1, T2).•Primary outcome: I-CAT score improvement at three months (T2).

Evaluates an enhanced educational intervention to improve IC acceptance and adherence.

Randomized controlled trial design with three follow-up time points (T0, T1, T2).

Primary outcome: I-CAT score improvement at three months (T2).

Specifications table

*This table provides general information on your protocol.*

**Table utbl0001:** 

**Subject area**	Medicine and Dentistry
**More specific subject area**	*Neuro-urology; nursing; rehabilitation*
**Name of your protocol**	A standardized educational Intervention to enhance acceptance and adherence to intermittent catheterization: Protocol for a multicenter randomized controlled trial (Serendipity protocol)
**Reagents/tools**	Not applicable; intervention consists of educational materials (informational booklet, video tutorial) and standard IC training. Catheters used include no-touch sheaths and protective tip catheters (manufacturer details per clinical setting).
**Experimental design**	A multicenter, parallel-group, randomized controlled trial (RCT) comparing standard clinical training with an enhanced educational intervention. Patients are randomly assigned to Group A (enhanced training) or Group B (standard training), with follow-ups at T0 (baseline), T1 (1 month), and T2 (3 months). The primary outcome is IC acceptance (I-CAT score at T2), with secondary outcomes including adherence (I-CAS), urinary symptoms (USQNB-IC), procedural autonomy (Autonomy Checklist), and satisfaction (QUEST).
**Trial registration**	This trial was registered at ClinicalTrials.gov (identifier: NCT07084376)
**Ethics**	The Comitato Etico Regione Toscana approved this study on February 4, 2025 - Area Vasta Centro (Ethical Committee of the promoting center, Azienda Ospedaliero-Universitaria Careggi, Firenze), protocol number: 27,679_spe. Written informed consent will be obtained from all participants before enrollment. The study follows Good Clinical Practice (GCP) guidelines, the Declaration of Helsinki, and EU GDPR for data protection.
**Value of the Protocol**	• To Provide a structured, evidence-based educational intervention to improve IC acceptance and adherence among male patients. • To Standardize IC training across multiple centers using validated tools (I-CAT, I-CAS, USQNB-IC, QUEST). • To Enhance patient self-management and autonomy by integrating behavioral health strategies, assistive technology, and patient-centered training approaches.

## Background

Intermittent catheterization (IC) is a widely used and clinically effective method for managing non-obstructive rinary retention and neurogenic bladder, particularly in individuals with spinal cord injuries, multiple sclerosis, and other neurological conditions [[1], [2], [3]]avoiding upper urinary tract complications and improving urinary symptoms, and quality of life [4,5]. However, despite its benefits, adherence to IC remains a significant challenge. Many patients struggle with psychological discomfort, procedural difficulties, and inadequate training, all of which can negatively impact their acceptance and consistent use of IC [6,7].

Educational interventions play a critical role in addressing these barriers and improving adherence to IC [4]. Existing studies highlight the importance of providing structured training to help patients integrate IC into their daily routines effectively [6,8]. However, the optimal method for educating patients remains undetermined, as educational practices vary widely across healthcare settings. There is currently no standardized approach to enhancing patient acceptance and adherence, underscoring the need for evidence-based educational strategies [2,4,7,9].

This protocol describes a multicenter, parallel-group, randomized controlled trial (RCT) designed to evaluate the effectiveness of an enhanced educational intervention for patients learning IC. The intervention consists of standard clinical training supplemented with an informational booklet and video tutorial to reinforce key concepts. The study will measure changes in IC acceptance using the Intermittent Catheterization Acceptance Test (I-CAT) alongside short-term adherence, urinary symptoms, functional autonomy, and patient satisfaction [10,11]. In other words, this protocol aims to provide a replicable methodology for improving IC training in clinical practice by standardizing and systematically evaluating this educational intervention. The results from this study may help to refine patient education strategies, ultimately improving adherence and patient-reported outcomes associated with IC [3,12].

## Description of protocol

### Study design

This study is a multicenter, parallel-group RCT conducted across 17 outpatient and hospital settings. The trial aims to evaluate the effectiveness of an enhanced educational intervention on IC acceptance compared to standard clinical practice training. Participants will be adult male patients (>18 years old) requiring IC training who meet the inclusion criteria and provide informed consent. This trial was registered at ClinicalTrials.gov (identifier: NCT07084376) before participant enrollment.

Participants will be randomly assigned (1:1) to the intervention group (Group A) or the control group (Group B) using a computer-generated list. Group A will receive standard clinical training plus an informational booklet and video tutorial, while Group B will receive standard training only.

The study follow-up period will be three months, with assessments conducted at three time points: baseline (T0), one-month post-initial training (T1), and three months post-initial training (T2). The primary outcome is the change in I-CAT scores, assessing patient acceptance of IC. Secondary outcomes include adherence to IC, urinary symptoms, procedural autonomy, patient-reported satisfaction, and functional abilities.

The study is open-label to both participants and investigators, as self-reported outcome measures will be used. However, the statistician analyzing the data will remain blinded to group assignments. Ethical approval has been obtained from institutional review boards, and all participants will provide written informed consent before enrollment. Data will be securely stored following GDPR regulations, with de-identified information retained for 15 years.

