### Sample size

The sample size for this study was determined to ensure sufficient statistical power to detect a meaningful difference in median I-CAT scores between the intervention and control groups. The primary endpoint aims to demonstrate an improvement in median I-CAT scores from 3.0 to 3.5, which corresponds to an increase from the median acceptance score to the 75th percentile of the previously reported distribution [10,11].

To achieve this, a significance level of 0.05 (5 %) was selected, meaning there is a 5 % probability of a Type I error, where a difference is incorrectly concluded when none exists. A power of 80 % (0.80) was chosen, ensuring that the study has an 80 % probability of detecting a true difference between the groups if one exists, thereby reducing the risk of a Type II error. Based on previous studies and pilot data, a standard deviation of 1 was assumed for the calculation [10,11]. Given these parameters, the sample size calculation was performed using a non-parametric (Mann-Whitney U) test to compare the two independent groups.

The formula used for calculating the required sample size accounts for effect size, significance level, and power. The required sample size per group, denoted as n, is calculated using the equation:(1)$$n=\frac{{\left(Z_{\alpha /2}+Z_{\beta }\right)}^{2}\times \;2\;\times \sigma^{2}}{\Delta^{2}}$$

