### Primary endpoint

The primary endpoint of this study is the improvement in median I-CAT scores at T2 (three months post-initial training), assessing IC acceptance. A 0.5-point increase in the median I-CAT score (from 3.0 to 3.5) represents a shift from the median to the 75th percentile of the previously reported distribution [10,11]. This reduction in IC-related reluctance is considered clinically meaningful, indicating a higher level of acceptance among participants receiving the enhanced educational intervention compared to those undergoing standard clinical practice training. The study is powered to detect this difference at T2, with 80 % power and a 5 % significance level, ensuring that the observed effect is both statistically and clinically significant.

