Self-report assessments will be administered to evaluate different aspects of the patient’s experience, adherence, and outcomes related to IC. All measurement tools selected for this study are supported by evidence of validity and reliability:(a)The Intermittent Catheterization Acceptance Test (I-CAT) will be administered at baseline (T0), one month post-initial training (T1), and three months post-initial training (T2). The I-CAT is designed to measure changes in acceptance rates of IC over time. It evaluates psychological comfort, willingness, and overall acceptance, helping to assess how well patients adapt to the procedure and the impact of educational interventions on their acceptance levels [10].(b)The Urinary Symptoms Questionnaire for Neurogenic Bladder in IC (USQNB-IC) will be conducted at T0, T1, and T2. This instrument evaluates urinary symptoms in patients with neurogenic bladder undergoing IC. It measures the severity and frequency of symptoms, including incontinence, urgency, and discomfort, allowing for the monitoring of symptomatic changes and potential improvements in urinary health with consistent IC use [14].(c)The Intermittent Catheter Adherence Scale (I-CAS) will be administered at T1 and T2 to measure adherence to the prescribed IC regimen. This tool assesses the frequency and consistency of catheter use as recommended by healthcare providers. Evaluating adherence through I-CAS will help identify barriers to consistent IC and assess the effectiveness of educational interventions in improving compliance [11].(d)The Autonomy Checklist will be completed at T0, T1, and T2 to assess procedural autonomy in IC. This checklist evaluates the patient’s ability to independently manage catheterization, including preparation, insertion, and hygiene maintenance. High scores indicate successful training and an increase in self-sufficiency in performing IC.(e)The Serendipity Questionnaire, developed by the researchers involved in this research, will be administered at T2 to capture subjective experiences and unexpected positive outcomes during the IC journey. This questionnaire includes items that explore patient insights, satisfaction, and any unexpected benefits they may have encountered. The qualitative data obtained will provide a richer understanding of the patient experience beyond clinical measures.(f)The Quebec User Evaluation of Satisfaction with Assistive Technology (QUEST) will be administered at T1 and T2 to assess patient satisfaction with the assistive devices used for IC. This instrument includes questions about the ease of use, effectiveness, and overall satisfaction with the catheter and related equipment. By identifying areas for improvement in device design and patient training, QUEST ensures that tools meet the practical needs of patients [15].(g)Motor function assessments will also be included in the study. The Motor Assessment using a Dynamometer will be conducted at T0 and T1 to measure grip strength, an essential factor in the ability to perform IC independently [16]. This test will help determine whether physical limitations may impact a patient’s ability to handle and use the catheter effectively by evaluating motor strength. The Manual Dexterity Assessment using the Nine Hole Test will be performed at T0 and T1 to measure fine motor skills, which are crucial for successful IC execution [17]. This test requires participants to place and remove pegs from a board, providing a quantitative measure of hand function. It will help identify patients who may require additional support or adaptive techniques to manage IC effectively.

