
### Statistical plan

The statistical analysis of this study will begin with descriptive statistics to summarize the baseline characteristics of participants, including sociodemographic and clinical data, under intention-to-treat analysis. Continuous variables will be presented using means, medians, standard deviations, and interquartile ranges, depending on their distribution. Categorical variables will be summarized using frequencies and percentages.

Inferential statistical analyses will be conducted to compare outcomes between the enhanced educational intervention group and the standard clinical practice training group. Independent *t*-tests will be used to compare normally distributed continuous variables, while Mann-Whitney U tests will be applied for skewed distributions and for the primary outcome (I-CAT score at T2). Chi-square tests will be used to compare categorical variables between the study groups.

Correlation analyses will be conducted following these comparisons to explore relationships between key study variables. Specifically, associations between IC acceptance scores (I-CAT), adherence levels (I-CAS), urinary symptoms (USQNB-IC), and functional abilities (Autonomy Checklist and motor assessments) will be examined. Depending on the distribution of the data, either Pearson’s correlation coefficient (for normally distributed variables) or Spearman’s rank correlation coefficient (for non-normally distributed variables) will be used. These analyses will help identify how different aspects of the patient experience and clinical characteristics interrelate, providing insight into the factors influencing IC acceptance and adherence.

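### The Study design section makes change in I-CAT the primary outcome, while the specifications table and the Statistical plan make it the I-CAT score at T2, the variable the sample size fits

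*Protocol article*

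**What the plan says.** The protocol article describes its primary outcome in five places.

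- Study design: "The primary outcome is the change in I-CAT scores, assessing patient acceptance of IC". No visit is named, and nothing says what the change is measured from.
- Specifications table: "The primary outcome is IC acceptance (I-CAT score at T2").
- Statistical plan: "Mann-Whitney U tests will be applied for skewed distributions and for the primary outcome (I-CAT score at T2"). This is the only place that ties a variable to a test.
- Primary endpoint: "The primary endpoint of this study is the improvement in median I-CAT scores at T2".
- Abstract: "Primary outcome: I-CAT score improvement at three months (T2").

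The Measurements section says that the I-CAT "will be administered at baseline (T0), one month post-initial training (T1), and three months post-initial training (T2"), so a change from baseline can be calculated. The Sample size section plans for "an improvement in median I-CAT scores from 3.0 to 3.5". It divides the difference between two medians by an SD of 1, sets two-sided alpha at 0.05 and power at 80%, and arrives at 64 per group.

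**The concern.** The T2 score and the change from T0 to T2 are different variables. Under randomisation both target the same expected mean difference between groups. They differ in variance, in how they respond to a chance imbalance at baseline, and in the difference of medians. A Mann-Whitney U test on one can reach significance while the same test on the other does not.

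Two things are at stake. First, if the primary variable is not settled before results are known, either could be defended from the text afterwards, and the 5% error rate would no longer hold. Second, a sample size worked out for one variable need not suit the other.

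**Working it through.** **Step 1: reproduce the planned number.** The inputs, from the Sample size section, are difference 0.5, SD 1, Z values 1.96 and 0.84.

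n per group = (1.96 + 0.84)² × 2 × 1² / 0.5² = 7.84 × 2 / 0.25 = 62.7, so 63.

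The two-sample t-test (noncentral t) gives 63.8, so 64. The stated 64 per group reproduces for a comparison of scores at one visit, with t-test power of 80.1%. Allowing for the efficiency of Mann-Whitney under normal data (factor π/3) gives about 66 per group, or 79% power at 64. That is close enough not to matter here.

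**Step 2: which variable do these inputs describe?** The difference of 0.5 is the gap between the median and the 75th percentile of a reported I-CAT distribution, and the effect size is a difference between two medians divided by the SD. The SD of 1 is attributed to previous studies and pilot data. The section does not say whether it is the SD of a score or of a change. Reading it as the SD of a score is an inference, though a natural one, because no SD of change and no T0-T2 correlation appear anywhere.

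**Step 3: what if change were analysed?** Assume SD 1 at both T0 and T2, correlation r between them, and the same 0.5 difference. Neither r nor the equality of the SDs is in the protocol article. Then

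SD of change = √(2(1 − r)).

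| r (assumed) | SD of change | n per group for 80% power (normal formula) | t-test power at 64 per group |
|---|---|---|---|
| 0 | 1.41 | 126 | 51% |
| 0.2 | 1.26 | 101 | 60% |
| 0.3 | 1.18 | 88 | 66% |
| 0.4 | 1.10 | 76 | 73% |
| 0.5 | 1.00 | 63 | 80% |
| 0.6 | 0.89 | 51 | 88% |
| 0.7 | 0.77 | 38 | 95% |
| 0.8 | 0.63 | 26 | 99% |

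The two variables need the same sample only at r = 0.5. Below that, change needs more than planned; above it, less.

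**Step 4: how often would the choice matter?** I simulated normal data with SD 1 at both visits, 64 per group, r from 0.2 to 0.7 and 20,000 trials per setting, and ran a Mann-Whitney U test on each variable. With no true effect, each test rejected in about 5% of trials, and at least one rejected in about 9%. With a true difference of 0.5, the two tests disagreed on significance in about 22% (r = 0.7) to 30% (r = 0.2) of trials.

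**Step 5: baseline adjustment, for reference.** In a linear model of the T2 score on group and T0 score, the residual SD is √(1 − r²). By the normal formula, the required n is 63 per group at r = 0, 48 at r = 0.5 and 33 at r = 0.7. It never exceeds the planned number.

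**The case against.** The strongest reply is that the plan has only one fully specified primary analysis. The Statistical plan names variable and test together, and the specifications table agrees. The Sample size section is written for two independent groups and a difference between two medians. The Primary endpoint section uses the loose word improvement, but it goes on to compare the enhanced arm with standard training and says that the trial is powered for that difference at T2. No section gives a test, an SD or an effect for change. The Study design sentence is then a single overview statement out of line with the rest. This stands, and it settles which definition should be kept. It does not remove the contradiction: the Study design section states a different primary outcome in plain terms, and the wording in the Abstract does not overrule it.

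A second reply is that the analysing statistician is blinded and that the trial is described as registered before enrolment. Both lower the risk of choosing after the fact. The registry entry and any separate SAP are not at hand and may already fix the variable. Blinding to group does not itself decide which variable is primary.

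A reader might go further and infer that the trial is underpowered, or that its SD is wrong. The documents do not support that. The stated number is right for the T2 score, and for change the shortfall arises only if r is below 0.5 (with equal SDs), which nothing in the article shows. Nor do they support saying that the trial has two rival planned analyses, or that anyone intends to choose between them.

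**Conclusion.** The inconsistency is real and is in the current text. The Study design section makes change in I-CAT primary, and the specifications table and Statistical plan make the T2 score primary. The weight of the document, including the sample size, lies with the T2 score. No planned number is shown to be wrong.

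If change were used instead, power at 64 per group would run from about 60% at r = 0.2 to 95% at r = 0.7. This assumes SD 1 at both visits, a 0.5 difference and a t-test. A free choice between the two variables would raise the type I error from 5% to about 9% under the simulated conditions. That figure shows what an unsettled definition could cost; it is not evidence that a choice will be made. Because the point concerns the primary outcome, it should be settled before any outcome data are compared by group.

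**What to change.** Use one definition in the Abstract, specifications table, Study design, Primary endpoint and Statistical plan: the primary endpoint is the I-CAT score at T2, compared between groups. Remove change in I-CAT as the primary outcome from the Study design section, list change from T0 as descriptive only, and replace the looser improvement wording in the Abstract and Primary endpoint sections.

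Then choose one of two routes for the analysis.

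- Keep the Mann-Whitney U test on the T2 score, with no mention of a covariate. The sample size section needs no change.
- Adjust for the T0 I-CAT. The Mann-Whitney U test takes no covariate, so the Statistical plan would have to replace it as the primary test with a model that does, such as ANCOVA of the T2 score on group and T0 score, or a proportional-odds model. Mann-Whitney can stay as a sensitivity analysis. Adding the covariate while leaving Mann-Whitney as the primary test would create a new contradiction.

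If the sponsor does intend change to be primary, the Sample size section must state the SD of change, or the T0-T2 correlation, and be reworked.

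The cost is a wording correction. No new data are needed, since the T0 I-CAT is already collected, and under a linear model with SD 1 the adjusted analysis needs no larger sample.

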### Settings

The study will be conducted in both outpatient and hospitalized settings across multiple centers, ensuring a diverse patient population and enhancing the generalizability of the findings. The coordinating center for this study is the Azienda Ospedaliero-Universitaria di Careggi in Firenze, which will oversee the study’s implementation, adherence to the protocol, and data collection processes across all participating sites.

This list includes centers that have expressed their commitment to the study, but it is not exhaustive. Additional centers may join as the study progresses, and any updates regarding participating institutions will be incorporated into the protocol accordingly.

### Participant recruitment and eligibility

Patients referred for IC training will undergo an initial screening to determine their eligibility based on predefined inclusion and exclusion criteria. Those who meet the eligibility requirements will be invited to participate and provided with comprehensive information about the study. Written informed consent will be obtained from all eligible participants before enrollment. Once consent is obtained, baseline data collection will be conducted, including sociodemographic information, clinical history, and prior experience with IC.

The study will include naïve patients who require training in IC using aseptic techniques, specifically focusing on using no-touch sheaths and protective tip catheters. Naïve patients are defined as those with no prior experience or training in aseptic IC or those with minimal experience (less than one month) who require structured education to perform the procedure safely. No-touch sheaths and protective tip catheters are designed to minimize contamination risks and enhance safety during catheterization. Eligible participants must be fully informed of all available catheterization devices and must voluntarily choose to use no-touch sheaths and protective tip catheters. The study will focus on adult male patients aged 18 years and older who must be capable of providing informed consent. Additionally, all participants must demonstrate a willingness to utilize no-touch sheaths and protective tip catheters as part of their educational intervention.

Exclusion criteria include cognitive impairments that may hinder comprehension of the training process, a history of anxiety, depression, or other psychiatric disorders that could impact adherence, and language barriers preventing understanding of written and verbal Italian instructions. Patients with learning difficulties affecting their ability to follow medical instructions, those diagnosed with urinary tract neoplasms or penile/urethral anomalies, and those requiring two or fewer catheterizations per day—making them unsuitable for adherence evaluation—will also be excluded from the study.

